**Methods/design:**

This will be a randomized crossover pilot clinical trial with a participant study duration of 28 days. The crossover nature allows each patient to serve as their own control. Briefly, patients presenting at a tertiary medical center’s Ambulatory Infusion Center (AIC) will be randomized to either: (1) receive an RBC transfusion as scheduled (transfusion) or (2) abstain from the scheduled transfusion (no transfusion). After an appropriate washout period, participants will crossover from the transfusion arm to the no-transfusion arm or vice versa. Activity levels will be recorded continuously throughout the study using an accelerometry monitor. In addition to device data, functional status and health outcomes will be collected via a weekly telephone interview. The primary outcome measure will be daily energy expenditure. Performance metrics, such as step count changes, will also be evaluated. Additional secondary outcome measures will include daily sedentary time and Patient-reported Outcomes Measurement Information System (PROMIS) Global 10 Survey scores.

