### Intervention

Those randomized to transfusion will receive the standard-of-care-ordered RBC transfusion. This means that they will receive the transfusion as specifically ordered by their primary physician, typically one to two units of allogeneic RBCs. Those randomized to the no-transfusion arm will be discharged from the AIC without receiving an RBC transfusion. The patients who are randomized into the transfusion group will be crossed over into the no-transfusion group and the patients who are randomized into the no-transfusion group will be crossed over into the transfusion group at a subsequent visit. The time of this crossover for a given patient will be at their next scheduled transfusion that is no less than 1 week from the time of their most recent RBC transfusion in this trial.

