### Primary analysis

The primary outcome analyses will be performed using an “as treated” rather than an “intention-to-treat” analysis set while accounting for the crossover design. This approach is most appropriate for this pilot clinical trial, which primarily aims to understand home functional status as it relates to ambulatory RBC transfusion. For statistical comparisons, we will fit a random effects model that utilizes daily total energy expenditure as the dependent variable and days from transfusion or control visit (“placebo” visit where no transfusion was performed). For simplicity, we will include the mean daily measurements for the 3 days prior to the transfusion/control visit as covariates in the model, and consider the 7 days after transfusion/control visit in the model. This censoring of data beyond 7 days after the transfusion/control visit is to avoid carryover effects with the model. We will test the transfusion indicator by study day interaction, with adjustment for baseline activity, for the primary hypothesis. This parameter will quantify how the profile of activity differs with and without transfusion while accounting for the variation in activity between participants by means of the random effect and baseline adjustment. Contrasts will be constructed to quantify the difference in the change in activity between these visits.

Sensitivity analyses will attempt to model the change in activity levels in the days after transfusion. These exploratory models will consider a potential initial boost in activity with linear or exponential trends to account for the change in activity over the 7 days after transfusion. These models will also include subject random effect and account for time-series correlation. These analyses will be expanded to include all data measured over the 28-day period.

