### Secondary endpoint analysis

Secondary endpoints measured by the accelerometer will be modeled similarly to the primary outcome measure. The association of the PROMIS Global 10 Survey score and activity will be quantified by the rank order correlation of the area under the curve for the incremental gain in activity over the 7 days (mean of the 7 days after transfusion/control visit minus the mean of the 3 days prior to the transfusion/control visit) and the PROMIS Global 10 Survey total score. We will conduct this on the entire data (transfusion and control visits) as well as with a partial correlation controlling for whether a transfusion was actually conducted.

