In addition to the above concerns about efficacy and safety, it is important to remember that blood products are a precious resource. Considering data from 2011 [1], the available supply of whole blood/RBC units exceeded the number of transfused units by only 5.2%, with a trend in donation rates dropping 3–4% per year. An aging US population can only be expected to exacerbate the situation. Furthermore, the direct and indirect costs associated with blood product transfusion are rising [52]. Goodnough et al. [36] found that over a 5-year period, implementing a best-practice alert triggered for higher Hgb transfusions saved a large hospital US$1.3 million annually in purchasing costs alone.

With the above in mind, it is clear that deeper understanding of the true utility of RBC transfusion is of vital importance to the field. The randomized crossover clinical trial proposed here aims to provide preliminary information on the feasibility of measuring the efficacy of RBC transfusion in improving home functional status with a wearable activity monitor. The study, while it can be described as a pilot, is robust in that it utilizes a randomized crossover design, incorporates an objective measurement of activity based on accelerometer data, and includes patient-reported health status. This study will provide novel data that will aid in the elucidation of transfusion’s influence on ambulatory activity following outpatient transfusion.

In addition to the strengths of the trial noted above, we also acknowledge potential weaknesses of the protocol. Such limitations include concerns relating to the detectability of activity level in what may often be a sedentary population with variable daily activity levels, risk that the effect from transfusion may exceed the 1-week washout period, and difficulty in recruiting patients who will be willing to consistently wear a monitor for 28 days. Though we acknowledge these potential challenges, the insights gleaned will greatly facilitate the potential design and conduct of a future, more definitive, clinical trial. We look forward to seeing the results of this trial and to gaining important insight into this clinically relevant question.

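### The 7-day cut-off does not keep carryover out of the second visit, and the 1-week minimum gap is counted only from an in-trial transfusion

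*Protocol article*

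**What the plan says.** All references are to the protocol article.

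- **Statistics, Primary analysis.** The model uses the 7 days after each visit and drops later days, with this reason: "This censoring of data beyond 7 days after the transfusion/control visit is to avoid carryover effects with the model". On baseline: "we will include the mean daily measurements for the 3 days prior to the transfusion/control visit as covariates in the model". The primary test is the interaction of transfusion with study day. In addition, "Contrasts will be constructed to quantify the difference in the change in activity between these visits". For the exploratory models: "These analyses will be expanded to include all data measured over the 28-day period".
- **Intervention.** Crossover takes place at the next scheduled transfusion that is "no less than 1 week from the time of their most recent RBC transfusion in this trial".
- **Abstract, Methods/design.** "After an appropriate washout period, participants will crossover from the transfusion arm to the no-transfusion arm or vice versa". No length is given there.
- **Discussion.** Among the limitations is the "risk that the effect from transfusion may exceed the 1-week washout period".
- **Secondary endpoint analysis.** A gain score ("mean of the 7 days after transfusion/control visit minus the mean of the 3 days prior to the transfusion/control visit") is rank-correlated with the PROMIS score.

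**The concern.** In a crossover, carryover is the part of the first visit's effect that is still present when the second visit is measured. Dropping days beyond day 7 discards late data within a period. It leaves in the second visit's own 7 days and its baseline, which is where carryover would be. The stated reason therefore credits the cut-off with something it does not do, and a reader could take the crossover estimates to be free of carryover.

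The second issue is the starting point of the 1-week minimum. A participant who begins without transfusion normally has no in-trial transfusion before crossover, so the rule as worded sets no minimum for that sequence. The crossover transfusion could then fall within the 7 days that are meant to represent no transfusion.

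At stake is the trustworthiness of the activity comparison that the article wants to read for an efficacy signal (Aims and objectives, Secondary).

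**Working it through.** **Plan's own figures.** The article gives no figure for carryover, decay or the distribution of gaps. Its sample size reproduces: 2 × 12 = 24, and 24 × 1.25 = 30. The point does not depend on it, except for the standard-error comparison in step 5.

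**1. Day counting, transfusion first.** Let g be the gap in days between visits; the Intervention section gives a minimum of 7.

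- Second window: days g+1 to g+7 after transfusion. At g = 7 this is days 8 to 14.
- Second baseline: days g−3 to g−1. At g = 7 this is days 4 to 6, entirely inside the first transfusion window.
- Baseline days shared with the first window at g = 7, 8, 9, 10, 11: 3, 3, 2, 1, 0.

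The 7-day cut-off removes none of these days.

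**2. Size for the primary interaction.** Assume that the effect on day d is e(d) = 2^(−d/h) with half-life h, that it starts at once, and that the two sequences are equal in size. Because decay is exponential, e(g+d) = f·e(d), with f = 2^(−g/h) the fraction left at the second visit.

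- Transfusion first: difference between visits on day d = e(d) − f·e(d) = (1 − f)·e(d).
- No transfusion first, with no overlap: e(d).
- Average over sequences: (1 − f/2)·e(d).

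The whole day profile shrinks by 1 − f/2, and so does the interaction.

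| f | share kept, 1 − f/2 |
|---|---|
| 0.10 | 0.95 |
| 0.25 | 0.875, about 0.88 |
| 0.50 | 0.75 |

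The visit baseline is constant over the days of a visit. With complete daily data it therefore does not change this interaction.

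**3. Direction for the baseline-adjusted change contrast.** Let D be the mean effect over days 1 to 7, Lp the mean residue in the second window, Lb the mean residue in the second baseline, and b the weight given to baseline. The average contrast is D − Lp/2 + b·Lb/2.

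Example with h = 7 and g = 7: D = 0.686, Lp = 0.343, Lb = 0.612.

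- b = 0: (0.686 − 0.172)/0.686 = 0.75 of the truth.
- b = 1: (0.686 − 0.172 + 0.306)/0.686 = 1.20 of the truth.
- No bias at b = Lp/Lb = 0.56.

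For h = 3, 7, 14, 28 days the neutral value of b is 0.27, 0.56, 0.75, 0.86, whatever the gap. The plan enters baseline as a covariate, so b is estimated from the data and could lie on either side.

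**4. Day counting, no transfusion first.** If the crossover transfusion comes k days after the control visit and k is below 7, then 7 − k days of the control window follow a transfusion. For example, k = 4 (arbitrary) leaves 3 such days. The article gives no distribution for k.

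**5. Precision of a first-period check.** With 12 per group, outcome variance σ² and within-person correlation ρ (assumed), the first-period variance is 2σ²/12 and the variance from 24 pairs is 2σ²(1 − ρ)/24. The standard-error ratio is √(2/(1 − ρ)) = 1.69, 2.00, 2.58 for ρ = 0.3, 0.5, 0.7.

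**The case against.** **The limitation is disclosed.** The Discussion admits that the effect may outlast a week. This stands as disclosure. It does not correct the reason given in the Primary analysis section, and it says nothing about the gap after a control visit.

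**The sentence has a narrower reading that works.** With visits at least 7 days apart, the cut-off stops one window from running into the next intervention. That is true, but it prevents overlap rather than carryover, and the Intervention section does not secure the 7 days for both sequences.

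**Crossover timing limits the residue.** Crossover is tied to the next scheduled transfusion, and standing orders usually trigger on low hemoglobin (Practice logistics and workflow). A short gap therefore suggests that the benefit has already faded. This stands. An effect that ended by day 7 would leave no carryover. A reader might infer losses of 35% to 42% by pairing a 7-day gap with half-lives of 14 or 28 days (f = 0.71 or 0.84), but those pairings fit badly with hemoglobin-triggered crossover.

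**A two-way washout may have been meant.** The abstract suggests so, the design figure is not available here, and the coordinator manages standing orders around the no-transfusion period. This stands against any claim that overlap will occur. It does not change what the Intervention rule says.

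**The go/no-go decision is not shown to shift.** A reader might infer that the gain score in the Secondary endpoint analysis inflates the efficacy signal. It feeds only a rank correlation with PROMIS and yields no comparison of transfusion with control. The decision on a larger trial also weighs feasibility, adherence and adverse events, and has no numerical threshold.

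**Conclusion.** The point holds and should be fixed. By day counting alone, the cut-off does not do what the text says it does, and the gap rule as written covers only one sequence.

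The size is less certain. Under exponential decay and equal sequences, the primary interaction is pulled toward zero by the factor 1 − f/2, a loss of 5% at f = 0.10 and 12.5% at f = 0.25. The article gives no f, and large values are unlikely. For the baseline-adjusted change contrast even the direction is unknown. The frequency of transfusions inside a control window is also unknown, so no trial-level bias can be attached to that part. The documents do not support a claim that carryover pushes the decision on a larger trial in a particular direction.

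**What to change.** 1. **Intervention.** Count the 1-week minimum from the first study visit in both sequences, with the over-riding transfusion criteria still applying. Cost: some crossover transfusions may be postponed by a few days in anemic patients. Recruitment has begun, so this changes trial conduct as well as wording.
2. **Primary analysis.** Replace the reason for the cut-off with: *The 7-day limit does not remove carryover from the first visit into the second.* Report the between-group comparison of days 1 to 7 in the first period as a check that is free of carryover between study visits. The sample size section already treats the first phase as a parallel-group comparison. Cost: about 1.7 to 2.6 times the standard error of the crossover contrast for assumed within-person correlations of 0.3 to 0.7, so it is a check and not a replacement.
3. **Sensitivity analyses.** Show the change contrast with and without the second-visit baseline. Where a transfusion falls inside a control window, also show the result with the window ended at that transfusion. State that this censoring may be informative, since patients who worsen are likely to be transfused sooner; for that reason it should not be the main analysis.

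Carryover bias stays in the crossover contrast after these changes, but it is stated and can be set against the first-period result.

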### Sample size considerations and recruitment

This is a pilot study to determine whether accelerometers are sensitive enough to detect change in functional status in patients undergoing ambulatory transfusion services. The primary hypothesis is to detect change in total energy expenditure after the transfusion in both between and within individual comparisons. A minimum clinically relevant difference is not yet known for this outcome. To estimate the sample size, we approach the calculation from the perspective of having sufficient data to estimate the standard deviation so that we could plan a follow-up study. Julious [27] recommends studying 12 participants per group for such aims. We apply this recommendation to this study by assuming that we want at least 12 participants to complete the first randomized phase of the crossover design (i.e., the parallel group portion of the study). Based on this, we will want to have at least 24 subjects who will provide evaluable data from the activity monitor. We therefore adjust the sample size upwards by 25% to account for attrition and/or changes in the transfusion schedule. Thus, our total planned sample size is 30 participants. Preliminary research with clinicians familiar with the infusion center patient population suggests that an enrollment of this size should be readily achievable. Specific strategies for achieving adequate enrollment include presentations to the hematology and oncology practices in order to advertise the study to providers, as well as access to the Mayo Clinic patient scheduling and electronic health record system. This will ensure the ability to have sufficient on-site recruiting staff on days where patients known to be eligible are scheduled for transfusion.

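### The primary model names only a between-participant random effect, so the between-visit contrasts (and a linear day interaction, if that is meant) would have standard errors that are too small

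*Protocol article*

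**What the plan says.** All of this is in the protocol article, Statistics, Primary analysis, unless noted.

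- Outcome and unit: "we will fit a random effects model that utilizes daily total energy expenditure as the dependent variable". The window is set by the instruction to "consider the 7 days after transfusion/control visit in the model", which with two visits gives 7 × 2 = 14 daily values per participant.
- Covariate: "we will include the mean daily measurements for the 3 days prior to the transfusion/control visit as covariates in the model".
- Test and estimate: "We will test the transfusion indicator by study day interaction, with adjustment for baseline activity, for the primary hypothesis", followed by "Contrasts will be constructed to quantify the difference in the change in activity between these visits".
- Covariance: the only random effect described has the stated job of "accounting for the variation in activity between participants by means of the random effect and baseline adjustment". The section also says that the analysis takes the crossover into account, but not how.
- Sensitivity models, next paragraph: "These models will also include subject random effect and account for time-series correlation".
- Sample size section: "we will want to have at least 24 subjects who will provide evaluable data from the activity monitor".

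Neither paragraph mentions a participant-by-visit effect, and neither says whether study day is linear or categorical.

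**The concern.** Transfusion or no transfusion is given once per visit, and seven daily values follow. Two sources of dependence within those seven days are not captured by a participant intercept. One is a shared good or bad week: the protocol's weekly calls ask about illness and injury for this reason. The other is correlation from one day to the next. The authors recognised the second, but named it only for the exploratory models.

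The quantity most exposed is the one Specific aim 1 describes, the change in mean daily activity over 7 days, which the contrasts estimate. The Secondary aims section says that strong evidence for transfusion would make a larger trial less likely. An interval that is too narrow could therefore influence that decision in either direction. Secondary accelerometer endpoints are to be modelled in the same way and would share the problem.

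**Working it through.** **The plan's own figure.** 12 per group × 2 = 24 evaluable; 24 × 1.25 = 30. This reproduces and does not depend on the covariance structure.

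**Inputs.** From the protocol: n = 24, 2 visits, 7 days per visit, 3 baseline days. Assumed, because the protocol gives no values: λ = visit variance divided by daily variance, 0.1 to 0.5; ρ = AR(1) correlation between successive days, 0.2 to 0.5. Daily variance is set to 1.

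**Step 1: between-visit contrast, visit variance only, baseline catching none of it.** The true variance of the difference in 7-day means is proportional to T = 1 + 7λ. A participant intercept with independent residuals uses instead the pooled residual variance (ignoring a few degrees of freedom for day terms)

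s² = [12n + (n − 1)T] / (13n − 1) = (288 + 23T) / 311.

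SE ratio (model/true) = √(s²/T). Actual size ≈ 2{1 − Φ(1.96 × ratio)}.

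| λ | T | s² | SE ratio | actual size |
|---|---|---|---|---|
| 0.1 | 1.70 | 1.052 | 0.79 | 12% |
| 0.25 | 2.75 | 1.129 | 0.64 | 21% |
| 0.5 | 4.50 | 1.259 | 0.53 | 30% |

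**Step 2: the same, with the visit deviation already present in the 3 baseline days.** Adjustment leaves λ′ = λ − λ²/(λ + 1/3) = λ/(1 + 3λ), that is 0.077, 0.143 and 0.200. Then T = 1.54, 2.00 and 2.40; SE ratio = 0.82, 0.73 and 0.68; actual size = 11%, 15% and 18%.

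**Step 3: serial correlation only.** Let S = 7 + 2Σ(7 − k)ρᵏ, k = 1 to 6. Then T = S/7, the within-visit mean square is w = (7 − T)/6, and s² = (288w + 23T)/311. For a linear day interaction, the true variance factor is V = c′Rc/28, where c = (−3, …, 3) and R is the AR(1) matrix; the SE ratio is √(s²/V).

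| ρ | S | T | s² | contrast: ratio, size | V | linear day: ratio, size |
|---|---|---|---|---|---|---|
| 0.2 | 9.88 | 1.41 | 0.967 | 0.83, 10% | 1.24 | 0.88, 8% |
| 0.3 | 11.78 | 1.68 | 0.945 | 0.75, 14% | 1.36 | 0.83, 10% |
| 0.5 | 17.03 | 2.43 | 0.885 | 0.60, 24% | 1.54 | 0.76, 14% |

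**Step 4: the interaction under visit variance.** A constant visit deviation cancels from any comparison of days within a visit, so V stays at 1 while the model uses s² above 1. The SE ratio is √1.052 = 1.03 to √1.259 = 1.12: standard errors too large, not too small.

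**Step 5: simulation with the baseline covariate.** Null trials, 24 × 2 × 7 values, participant intercept and independent residuals, 1,500 runs per setting, visit deviation starting after baseline:

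- Contrast: 10%, 20%, 31% for λ = 0.1, 0.25, 0.5; 10%, 14%, 25% for ρ = 0.2, 0.3, 0.5; 40% with both at 0.5.
- Linear transfusion-by-day: 8%, 10%, 14% for the same ρ; 2 to 4% under visit variance alone (λ up to 1.0).
- Categorical transfusion-by-day (6 df): 4 to 5% under serial correlation alone; from 5% down to 0.4% under visit variance alone.

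A further null simulation gave 10 to 17% for the contrast at λ of 0.1 to 0.5, close to Step 2. The gap between 17% and 31% at the upper end is explained by how much of the visit deviation the baseline days pick up.

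**Step 6: analyses that respect the correlation.** Participant-level paired versions of all three tests (baseline-adjusted difference in visit means, difference in slopes, Hotelling T² on six day contrasts; 5,000 runs per setting) gave 4.4 to 5.4% in every setting tried.

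**The case against.** The strongest objection is that this reads too much into a condensed article. The text does not say that residuals are independent. It says that the crossover is taken into account. The word *also* in "These models will also include subject random effect and account for time-series correlation" could mean that the primary model has these features too. Covariance details often sit in an analysis plan, and none is shown. This stands in part: the concern is conditional on the model being fitted as described. But the section does state a covariance approach, gives its random effect a single purpose, and raises serial correlation only for the exploratory models, so it does more than leave the matter open.

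The second objection is that the declared test is the interaction with day, not the mean contrast. This stands, and it limits the point. A reader might infer that every primary test has standard errors that are too small. The documents do not support that: visit variance makes the interaction conservative, and with categorical day no inflation appeared in any setting. Linear and exponential trends are mentioned only for the sensitivity models, so categorical day is a fair reading of the primary one.

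Three other inferences also go too far:

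- The seven days are not treated as fully independent. They are independent only given the participant effect and a visit-specific baseline.
- The sensitivity models do not repair within-visit dependence as a whole. They name serial correlation but no visit effect.
- The documents do not show that the follow-up trial would be undersized. The sample size section ties the standard deviation to the parallel first phase and does not say that this model's residual would be used.

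**Conclusion.** The concern holds for the between-visit contrasts, which carry the Aim 1 effect, and for a linear day interaction if serial correlation is positive. As described, the model would turn a nominal 5% into roughly 10 to 25% for the contrasts, about 30% where a visit variance of 0.5 arises wholly after baseline, and more if both sources are strong. For linear day the figure is about 8 to 14%. For categorical day the test is nominal or conservative, at some cost in power.

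The direction for the contrasts is the same at every non-zero setting tried. The size rests entirely on assumed λ and ρ, and on the model being fitted with a participant intercept alone. The sample size of 30 is not in question.

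**What to change.** In the Primary analysis section, specify for the primary model:

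- a participant random intercept and a participant-by-visit random intercept;
- a serial residual correlation within visit, for example AR(1);
- small-sample degrees of freedom, for example Kenward-Roger;
- whether study day is linear or categorical.

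Name the fallback in advance: if that model does not converge, use the baseline-adjusted paired comparison of 7-day visit means. Report the participant, visit and day variance components, so that the follow-up trial can be planned on the one that matches its design.

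Cost: a change of analysis wording only, with no change to data collection or to the 30 participants. Contrast intervals widen by the inverse of the SE ratio: about 1/0.82 = 1.22 to 1/0.68 = 1.47 times when the baseline catches part of the visit deviation, 1/0.64 = 1.56 at λ = 0.25 when it catches none, and 1/0.53 = 1.89 at the extreme. The fuller model may be hard to estimate with about 24 participants, which is why the fallback should be fixed beforehand.
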